### Inclusion criteria

The inclusion criteria will be the following:
Children aged between 2 and 16 years old.American Society of Anesthesiologists physical status classification grades I and II.Informed consent (IC) signed by parents or legal guardians of the minors.Specific informed consent for children aged between 12 and 16 years old.No confirmed allergies to antihistamines.

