### Randomisation

Following signature of the IC by the legal guardians of the minors and/or the child’s agreement (if applicable), randomisation to treatment with/without hydroxyzine will be performed. Randomisation will occur in a 1:1 ratio in blocks of 8. The non-blinded nurse will randomise subjects with electronic case record form (REDCap). The sequence will be blinded to all team members.

Accompaniment by clowns ([name] from Fundacion Theodora) will depend on the clown presence/availability on the day of the intervention. An alphabetical code will be assigned to patients assigned to clown accompaniment (A) or not (B).

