### Variables

#### Demographics

Age, sex, underlying pathology and the type of surgery will be collected.

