#### Outcome measures

POA assessment: All subjects included in the study will be filmed at four moments to later evaluate their POA by the m-YPAS scale.Saliva and blood cortisol determination: Patients’ saliva will be collected by Salivette® device at time-points M1 and M2. Likewise, a 5-ml blood sample will be obtained at time-point M3 to determine blood cortisol levels after the induction of anaesthesia.Induction Compliance Checklist: It will be performed by the anaesthesiologists in the operating room.Assessment of anaesthetic recovery with or without presence of delirium using PAEDS (PediatricAnesthesia Emergence Delirium Scale) [21] and assessment of post-anaesthetic recovery in PACU using Aldrete [22].Vital signs on arrival at PACU and every 30 min until the transfer to general ward: heart rate and respiratory rate.Pain Scales: Multidimensional pain scale for children under 3 years old, face pain scale for children aged 4–7 years and Visual analog scale for children older than 7 years old.Need of postoperative analgesia.Time to hospital discharge after leaving the operating room, in minutes.Evaluation on perceived healthcare quality: to fulfil this objective, a self-administered satisfaction survey will be completed by patients and parents/legal guardians after anaesthesia recovery and once hospital discharge is indicated. Healthcare professionals that usually attend children submitted to Major Outpatient Paediatric Surgery and that are involved in the study will complete the survey when the study is finished. The survey used is elaborated following the general criteria established by the Madrid Health Service for the elaboration of citizen satisfaction surveys [23]. Paediatric patients under 5 years old or older patients and parents/legal guardians with cognitive impairment or difficulty in understanding the language, will be excluded from this evaluation.

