#### Data analysis

The analysis will be performed by protocol and intention to treat. The qualitative variables will be presented with their frequency distribution. The quantitative variables will be summarised with their mean and SD. The quantitative variables that show an asymmetric distribution will be summarised with the median and interquartile range.

Comparison of the baseline characteristics of the four study groups will be performed. The association between qualitative variables will be evaluated by Pearson’s χ^2^ test or by Fisher’s exact test. For quantitative variables, means will be compared with Student’s *t* test for independent groups or with nonparametric test for the quantitative variables if they do not fit a normal distribution.

For the main outcome (POA) and secondary quantitative variables evaluated, a repeated measures analysis of the variance (ANOVA) will be carried out. The Bonferroni correction method will be used for multiple comparisons.

A comparison of means in each time-point and of the interaction between the dependent variable of the analysis (test score) and the study group (inter-subject factor) will be assessed. If any baseline characteristics between groups present clinically relevant differences, the model will be adjusted by those variables. Qualitative variables will be compared between groups using Pearson’s χ^2^ test. The relative risk with 95% confidence intervals will be calculated. If any of the baseline characteristics between groups presents statistically significant and/or clinically relevant differences between the four study groups, odds ratio (ORs) will be estimated using a logistic regression model. For all tests, a significance level of 5% will be accepted. The analysis of the data will be done by the statistical package STATA 12.0.

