## Discussion

POA is observed amongst children during their stay in the operative room with a prevalence of 83.3% [23]. Adverse psychological and behavioural changes (decrease in children’s self-esteem and emotional well-being, increased anxiety, sleep disturbances and social isolation) have been observed in a rate of 25% in children during hospital stay and even at 1-year post-discharge [6]. A recent systematic review also identified negative psychological sequelae in children [18].

The search for an ideal premedication drug to reduce POA in children is ongoing. The drugs used as anxiolytics are not exempt of side effects and the studies about this issue are limited to dental procedures [14–16]. One study [15] evaluated hydroxyzine at doses of 0.15 mg/kg, yet the dose proposed in our clinical trial is of 2 mg/kg.

The role of clowns and hydroxyzine in the management of anxiety is controversial as there are studies both for and against them [18–20]. We have not found any study that determines the additive effect on anxiolysis of distracting techniques with clowns and pharmacological treatment, as we propose in our case.

The proposed study has some limitations. The clowns are not always at the hospital; therefore, assignment to this intervention depends on whether they are present or not on the day of surgery. In order to reduce this bias, the healthcare professionals that plan the patient’s surgery will not know when the clowns come to the hospital.

The main objective of this study is the evaluation of POA. Studies that evaluate POA are difficult to perform and interpret, mostly because of the difficulty in assessing anxiety attributable to the surgical act. According to some studies [3, 25], the moment with the maximum rate of anxiety and fear associated with the entire surgical procedure is during anaesthetic induction. Therefore, evaluating the child’s anxiety during anaesthetic induction is very useful to determine whether the strategies used in the presurgical period have been effective in reducing anxiety [26]. That is the reason why in the present study, POA is evaluated in both moments. Most studies on this topic use a presurgical anxiety rating scale, the m-YPAS [23, 24, 26, 27].

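### PACU heart rate and respiratory rate are compared across ages 2 to 16 without age unless a baseline difference is judged clinically relevant, which costs some precision (minor)

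*Protocol article*

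**What the plan says.** Under Outcome measures the article lists "Vital signs on arrival at PACU and every 30 min until the transfer to general ward: heart rate and respiratory rate". Under Data analysis it assigns the method: "For the main outcome (POA) and secondary quantitative variables evaluated, a repeated measures analysis of the variance (ANOVA) will be carried out". The same section then fixes when a covariate enters that model: "If any baseline characteristics between groups present clinically relevant differences, the model will be adjusted by those variables".

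The inclusion criterion for age is "Children aged between 2 and 16 years old", and the Demographics section says "Age, sex, underlying pathology and the type of surgery will be collected". Hydroxyzine is randomised 1:1 in blocks of 8, with no stratification by age mentioned. Nothing else in the article brings age into the vital-sign comparison, either as a fixed covariate or by standardising the readings for age.

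**The concern.** The rule makes adjustment depend on whether the groups happen to differ. What a covariate does for precision depends instead on how strongly it predicts the outcome, and that gain is there even when the groups are perfectly balanced. Heart rate and respiratory rate in children can be expected to fall with age. That is general physiology, which the article does not state, and an age range of 2 to 16 years leaves ample room for it. Without age in the model, the spread due to age stays in the error term.

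What is at stake is sensitivity. The abstract's conclusions say that the trial seeks the option with the best safety profile, and these two are the only vital signs listed. A comparison with more noise than necessary makes a real hydroxyzine effect on either of them harder to see, and makes a finding of no difference less informative.

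**Working it through.** **Inputs**
- Group size: 47 in each of four groups, 188 in total (Sample size section).
- Significance level: 5% for all tests (Data analysis), taken here as two-sided.
- Age-outcome correlation r: not in the documents. Assumed 0.3, 0.5 and 0.7, where r relates age to the level being compared (a reading, or the child's mean over readings).
- Power: 80%, chosen for illustration. The article claims no power for vital signs.

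**The plan's own figure.** The 47 per group was derived for the m-YPAS score. With a common SD of sqrt((13.5² + 24.2²)/2) = 19.59, a difference of 14.3, two-sided 0.025 and 90% power, the normal approximation gives n = 47 with power 0.903. The figure reproduces. It serves here only as the available group size.

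**Step 1: residual spread.** With age as a linear covariate and balanced groups, the residual SD is sqrt(1 − r²) times the unadjusted SD:
- r = 0.3: sqrt(0.91) = 0.954
- r = 0.5: sqrt(0.75) = 0.866
- r = 0.7: sqrt(0.51) = 0.714

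**Step 2: sample-size equivalent.** Leaving age out is like needing 1/(1 − r²) times as many children: 1/0.91 = 1.10, 1/0.75 = 1.33, 1/0.51 = 1.96.

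**Step 3: detectable difference at 47 v 47.** Unadjusted: (1.96 + 0.84) × sqrt(2/47) = 2.80 × 0.206 = 0.58 SD. Multiplying by the factors in step 1 gives the adjusted values.

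| Assumed r | Sample-size multiplier | Detectable, unadjusted | Detectable, age-adjusted |
|---|---|---|---|
| 0.3 | 1.10 | 0.58 SD | 0.55 SD |
| 0.5 | 1.33 | 0.58 SD | 0.50 SD |
| 0.7 | 1.96 | 0.58 SD | 0.41 SD |

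**Step 4: power for a true difference of 0.5 SD at 47 v 47.** Unadjusted, 0.5/0.206 = 2.42 and 2.42 − 1.96 = 0.46, which gives 68%. Dividing 2.42 by 0.954, 0.866 and 0.714 before subtracting 1.96 gives 72%, 80% and 92%.

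**Step 5: where this applies.** Data analysis plans both a comparison of means at each time-point and an interaction test. If age shifts a child's readings by the same amount throughout the PACU stay, that shift cancels within the child and largely drops out of the time-by-group test. The figures above therefore concern between-group comparisons of level only.

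**The case against.** The strongest reply is that nothing here is an error. An unadjusted comparison of randomised groups is valid, a conditional adjustment rule is a legitimate choice, and a condensed article may leave the covariates for each secondary variable to an analysis plan. Heart rate and respiratory rate carry no stated hypothesis: they are absent from the main objective and from the abstract's list of further assessments, and the Safety section relies on adverse events. At r = 0.3 the gain is slight (0.58 v 0.55 SD; 68% v 72% power).

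Most of this stands, and it limits the point to a minor one. It does not remove it. The article is not silent on covariates. It states a rule, and by that rule age stays out unless an imbalance is found. Always including age is better for these two measures and costs almost nothing.

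A stronger reading is tempting for the clown contrast. Clown accompaniment "will depend on the clown presence/availability on the day of the intervention", so it is not randomised, and a reader might infer that an age gap left unadjusted would produce false positives. The documents do not support that:
- The Discussion says that the professionals who plan the patient's "surgery will not know when the clowns come to the hospital", and the article gives no reason to expect clown days to draw younger or older children.
- If age gaps arise only by chance, the unadjusted test keeps its 5% level on average. Inflation appears only if one assumes a particular gap.
- With ages assumed uniform from 2 to 16, the age SD is 14/sqrt(12) = 4.04 years. Even if arms were pooled to 94 v 94, which the article does not state, the standard error of the gap is 4.04 × sqrt(2/94) = 0.59 years, so a chance gap of 1 year or more has a probability of about 9%.
- A large gap would probably trigger the plan's own adjustment, and "The Bonferroni correction method will be used for multiple comparisons".

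**Conclusion.** The point holds as a minor loss of precision on two secondary measures. Under the stated rule, PACU heart rate and respiratory rate are by default compared without age. For between-group comparisons of level at 47 v 47, the detectable difference is 0.58 SD, where the same data with age in the model would allow 0.55, 0.50 or 0.41 SD.

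The size rests on the assumed correlations of 0.3, 0.5 and 0.7, on age acting roughly linearly, and on 80% power at a two-sided 5% level. The direction needs only that age predicts these measures. The hydroxyzine comparison is not biased, no inflated false-positive rate is claimed for the clown contrast, and the m-YPAS result and the sample size are untouched.

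**What to change.** Add one sentence to Data analysis: PACU heart rate and respiratory rate will always be adjusted for age as a covariate fixed in advance (or analysed as age-standardised values), whatever the baseline comparison shows. State how age enters, for example as a linear term. The conditional rule can stay for other baseline characteristics.

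The cost is one sentence and about one degree of freedom (188 − 4 = 184 between children becomes 183 with a linear term). No new data are needed, because age and both vital signs are already collected.

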#### Safety

Adverse events will be carefully monitored throughout the study. All adverse events will be collected in the case report form for each subject, regardless of the causal relationship with study treatment. The investigator will notify, within 24 h, all serious adverse events, serious adverse reactions, unexpected adverse reactions, and serious and unexpected serious adverse reactions to the sponsor. If any information is not available at the time of notification, it will be completed within 7 calendar days with a follow-up report. The sponsor will promptly notify any information that could modify the benefit/risk ratio of the investigational drug or that determines changes in its administration schedule or in the performance of the trial.

#### Ethical approvals

The study has been approved by the Clinical Research Ethics Committee of the participating centre’s Hospital. The confidentiality of subject data will be maintained at all times in accordance with current legislation. All subjects and/or parents/legal guardians are informed about the study and will be asked for acceptance to participate in it. This study will be carried out following international ethical recommendations for conducting human research and clinical trials contained in the latest revision of the Declaration of Helsinki as well as those established in the Good Clinical Practice Guidelines and current legislation. All subjects will be supervised by qualified medical personnel during their participation in the study.

## Discussion

POA is observed amongst children during their stay in the operative room with a prevalence of 83.3% [23]. Adverse psychological and behavioural changes (decrease in children’s self-esteem and emotional well-being, increased anxiety, sleep disturbances and social isolation) have been observed in a rate of 25% in children during hospital stay and even at 1-year post-discharge [6]. A recent systematic review also identified negative psychological sequelae in children [18].

The search for an ideal premedication drug to reduce POA in children is ongoing. The drugs used as anxiolytics are not exempt of side effects and the studies about this issue are limited to dental procedures [14–16]. One study [15] evaluated hydroxyzine at doses of 0.15 mg/kg, yet the dose proposed in our clinical trial is of 2 mg/kg.

The role of clowns and hydroxyzine in the management of anxiety is controversial as there are studies both for and against them [18–20]. We have not found any study that determines the additive effect on anxiolysis of distracting techniques with clowns and pharmacological treatment, as we propose in our case.

The proposed study has some limitations. The clowns are not always at the hospital; therefore, assignment to this intervention depends on whether they are present or not on the day of surgery. In order to reduce this bias, the healthcare professionals that plan the patient’s surgery will not know when the clowns come to the hospital.

The main objective of this study is the evaluation of POA. Studies that evaluate POA are difficult to perform and interpret, mostly because of the difficulty in assessing anxiety attributable to the surgical act. According to some studies [3, 25], the moment with the maximum rate of anxiety and fear associated with the entire surgical procedure is during anaesthetic induction. Therefore, evaluating the child’s anxiety during anaesthetic induction is very useful to determine whether the strategies used in the presurgical period have been effective in reducing anxiety [26]. That is the reason why in the present study, POA is evaluated in both moments. Most studies on this topic use a presurgical anxiety rating scale, the m-YPAS [23, 24, 26, 27].

Additionally, cortisol levels in blood and saliva correlate with stress. Free fraction levels of cortisol in saliva are a faithful reflection of its serum levels and it increase in the same way when the patient is exposed to stressful situations that activate the axis. Therefore, in this study, in order to establish the effect of the different strategies to reduce POA, two different outcomes will be used, one objective (cortisol levels) and one subjective (m-YPAS).

In the reviewed studies, satisfaction surveys about healthcare quality are almost systematically carried out by parents [5, 6]. In addition, in many of them, the perception of the healthcare professionals involved is also requested, observing a disparate impact of the different POA management strategies depending on the professional questioned [9]. The present study will consider not only parents and professional opinion, but also children’s perception of the healthcare quality of the presurgical interventions to reduce POA.

If the hypothesis of this study is confirmed, the combination of clowns and hydroxyzine may be considered the most effective and safety option for the treatment of POA in children.

## Trial status

Subject recruitment started in 12th January 2018 and is ongoing, recruitment will be completed in 30th December 2019. Protocol version: 7 (1st April 2019).

## Data Availability

Regarding sharing materials and managing of intellectual property, data will be available on request to the authors.

## Abbreviations

IC: Informed consent
PACU: Post-Anaesthetic Care Unit
POA: Preoperative anxiety
